## Abstract

**Background:**

Chronic stress and emotional and cognitive regulation difficulties during early childhood are associated with risky behaviors and negative outcomes later in life. As preschoolers are at a developmental stage where their emotional and cognitive regulation skills are still emerging, they often rely on external support to manage their emotions and behaviors. Intervening early promotes healthy development and preventing adverse outcomes. Mindful movement practices (MMPs)—which incorporate physical activities, breathwork, and reflective exercises—show the potential to enhance emotional and behavioral skill regulation. However, the impact of MMPs on cognitive and social-emotional development in young children has not been thoroughly researched, and the underlying mechanisms remain unclear.

**Objective:**

This pilot randomized controlled trial aims to assess the feasibility and acceptability of implementing MMPs in preschool classrooms and explore their effects on preschoolers’ social-emotional, cognitive, and physiological development. The study also focuses on enhancing prosocial behaviors and reducing problem behaviors. This protocol paper outlines the research procedures, sample demographics, and survey data psychometric properties.

**Methods:**

The study was conducted in 3 preschool classrooms (2 intervention and 1 waitlist control). Data were collected among 32 children and 8 teachers. Before the study began, 8 formative focus groups were facilitated with 5 administrators and 33 teachers in total to inform modifications to the program and research design. The intervention group participated in a 16-week program that included neural-based drills, aerobic activities, breathwork, and “feelings circle” exercises, along with classroom and home kits. The waitlist control group received a shortened 8-week program after the intervention groups completed their sessions. Data were collected before the intervention, at the midway point of the intervention, and after the intervention and again 2 months after the intervention. Measures included behavioral tasks, biomarkers (heart rate variability via wearable sensors and hormonal substrates in hair), and surveys from parents and teachers. Implementation fidelity was assessed using quantitative logs, qualitative field notes, and video observations. Postintervention interviews and focus groups were conducted with teachers, parents, and administrators.

**Results:**

Formative focus groups were conducted with 33 teachers and 5 administrators. Behavioral task, biomarker, and survey data were collected from 40 participants, including 32 preschoolers aged 3 to 5 (mean 4.4, SD 0.64) years and 8 teachers with a mean age of 37.9 (SD 11.47) years. Postintervention interviews and focus groups were completed with 7 teachers, 4 administrators, and 8 parents.

**Conclusions:**

This paper describes study procedures. Future publications will present primary outcome findings and evaluate the feasibility and acceptability of this MMP and research design in community-based and university-based preschool settings. Future papers will explore the data to provide preliminary evidence for the program’s effectiveness, mechanisms of effects, and the need for larger randomized controlled trials to optimize early childhood mindfulness interventions.

**International Registered Report Identifier (IRRID):**

DERR1-10.2196/75731

## Introduction

### Background

Chronic stress is an increasing public health concern that often originates in early childhood, especially among vulnerable populations [1,2]. Chronic stress in early childhood—often referred to as early life stress or childhood adversity—is typically measured by adverse experiences such as abuse, neglect, or lack of resources (eg, Smith and Pollak [3]). Persistent stress during early childhood can lead to emotional and cognitive dysregulation, which may later result in risky behaviors during adolescence, including substance abuse, violence, delinquency, and unsafe sexual practices [4-6]. Such outcomes contribute to substantial social and economic burdens in adulthood, manifesting as increased interactions with the criminal justice system, addiction, unemployment, and various health issues [7-9]. Early childhood is a crucial period to develop positive coping strategies via the implementation of evidence-based interventions designed to foster positive trajectories in life.

Preschool years are a pivotal period for the maturation of brain regions associated with motor function, self-regulation, cognition, language, and social competencies [10]. The developmental changes occurring in early childhood present an optimal opportunity for intervention, with preschool environments serving as ideal settings for such initiatives. The traditional social-emotional learning (SEL) programs, such as the well-known Business As Usual program, are standardized programs that have been embedded in the daily routine and classroom curriculum (eg, literacy, math, and circle time), especially focusing on regulating classroom environments and instructional practices [11]. Such a program has been critiqued for limiting responses to individual developmental needs and impeding the integration of comprehensive and inclusive models [12].

Mindful movement practices (MMPs) extend beyond traditional SEL programs by adopting a more developmental and sensitive approach tailored to the unique needs of children. MMPs incorporate movement patterns, attention-focused exercises, breathwork, and static postures, providing effective self-regulation strategies for young children [13-15]. These practices leverage sensory motor systems, cognitive control, and emotional regulation skills to assist children in managing stress and emotional responses [16,17]. Furthermore, the SEL components inherent in MMPs foster positive emotional and behavioral development in children. There are several facets that make this MMP unique from other SEL programs. First, the MMP used in this study adopted a train-the-trainer approach, whereby teachers were trained by program implementers on how to implement the MMP outside of the planned programming schedule. This approach builds teachers’ capacity to implement the program independently. Furthermore, teachers were given calm corner kits to use in the classroom and parents received kits for children to use at home. Using this approach facilitated the reinforcement of learned mindfulness strategies and ensured the consistency of school-home environments to support children’s behavior. By training the teachers and providing calm corner kits, children have more opportunities across settings for SEL.

While most school-based mindfulness research has focused on adolescents, findings show limited effects on externalizing behaviors (eg, aggression) and modest impacts on internalizing behaviors (eg, anxiety) [18-20]. Randomized controlled trials (RCTs) are now emerging that investigate the effects of mindfulness in preschool-aged children [21-24] and the implementation of MMPs in early elementary settings [25]. These studies have shown improvements in self-control, motor function, behavior, executive function, and social-emotional competencies. In addition, MMPs have demonstrated feasibility in urban elementary settings, yielding enhancements in self-control, motor skills, and behavior [25]. Mindfulness practices tailored for preschoolers have also indicated positive outcomes in motor control and social-emotional functioning [21]. These published RCTs show the benefits of mindfulness among preschoolers and school-aged children, but they have not examined which children are most responsive to specific components of MMPs nor have they explored the underlying mechanisms that contribute to the observed changes. Further research is needed to understand the physiological and social-emotional mechanisms underlying MMP effectiveness including identifying which elements of MMPs are most effective for children from diverse racial, sociodemographic, and neurodiverse backgrounds.

Many studies have highlighted the positive impacts of mindfulness-based interventions in children, and there is a growing body of evidence that demonstrates benefits for teachers who participate in mindfulness-based educator training [26-29]. These include minimized teacher burnout, enhanced well-being and social-emotional competencies, cultivation of classroom climates more conducive to learning, teacher-student relationships, classroom management, and self-efficacy [26]. These findings are consistent with the prosocial classroom model, which suggests that teachers’ social-emotional skills and well-being have a positive impact on their relationship with children and classroom management [30]. To our knowledge, no study has examined the effects of mindfulness-based classroom interventions on teacher outcomes. For example, changes in children as a result of mindfulness-based interventions may lead to improved teacher outcomes as mentioned earlier, student-teacher relationships, and attunement in physiological responses.

In response to these gaps, we conducted a pilot RCT to evaluate the hypothesis that MMPs could alter preschoolers’ behavioral difficulties by impacting physiological, social-emotional, and cognitive factors, which, in turn, could affect teacher outcomes. This preliminary evidence will provide support for using these assessments in a future full-scale RCT.

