#### Effects on Mechanisms and Outcomes

This aim focused on investigating how the implementation of the MMP influences self-regulatory capacities, SEL skills, problem behaviors, and prosocial behaviors, as well as identifying underlying physiological mechanisms of program effects at the midpoint, postintervention time point, and 2-month follow-up. Physiological data were collected after each MMP component, allowing for the evaluation of the effects of sequential implementation on physiological responses.

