#### Data Collection Timeline

Data were collected at 4 time points: baseline (preintervention; all classrooms), midintervention time point (8 weeks into programming; all classrooms), postintervention time point (immediately following the 16-week intervention or waitlist period; all classrooms), and 2-month follow-up (2 months after the intervention; 1 intervention classroom). In the waitlist control group, the postintervention time point also served as their second baseline and the 2-month follow-up served as their postintervention time point (immediately after the 8-week intervention). The data collection time points are illustrated in Figure 1 for the intervention (black) and waitlist control (gray) groups. At each time point, survey data were collected electronically (in person or online) or via paper and pencil, whichever was feasible and preferred by participants. Behavioral assessments were administered at all time points except for the midintervention time point.

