##### HRV Measurement

HRV assesses acute stress response and reflects the balance between the sympathetic nervous system and parasympathetic nervous system, both of which are integral to maintaining homeostasis [51]. HRV is a well-established biomarker of an individual’s ability to regulate and recover from stress [52].

For teachers and children who opted into this component of data collection, HRV data were collected at multiple time points: before the intervention, every 4 weeks during implementation (with each new module), and at postintervention and 2-month follow-up assessments. To collect HRV data, trained research assistants attached Firstbeat Body Guard sensors (Firstbeat Technologies Ltd [53]) to the participants—both children and teachers—by placing them beneath the right collarbone and connecting the sensor cable to the rib cage on the opposite side [54]. If a participant had sensitivities to its placement on the front of the body, electrodes were placed in these equivalent locations on the back. The sensors were removed once data collection was complete.

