##### Hormone Measurements

Hair was collected to measure cortisol, testosterone, and dehydroepiandrosterone (DHEA) levels to capture chronic stress and threat-challenge exposure. Cortisol, a hormone secreted by the HPA axis, is known to rise in response to stress [57]. Testosterone, produced by the HPG axis, also increases in response to challenging situations [58,59]. DHEA is closely linked to both cortisol and testosterone and is needed to tease out the unique coupling effect. DHEA is produced adrenally in both the gonads and the brain. DHEA and its sulfated analog are the most abundant hormones in the body, and as an adrenal androgen, DHEA operates as an end-product of both HPA and HPG axes [60]. By examining the coupling of HPA and HPG axes activity, both independently and together, we can better predict the risk of negative health outcomes related to stress [61]. In addition, exploring HPA and HPG coupling broadens the understanding of stress from the traditional “fight-or-flight” response to a more nuanced “threat-challenge” framework, which can apply to a wider range of real-world stressors [58,62].

Hair samples were collected from both children and teachers who consented to participate in this component of the study. These samples were used to assess cortisol, DHEA, and testosterone levels, as hair is highly sensitive to hormonal changes. Hair sampling is more feasible than saliva collection in preschool-aged children, and hormone measurement is more reliable in hair than fingernail clippings. Hair samples were collected at 3 time points: preintervention, postintervention, and 2-month follow-up time points. A 1-cm section of hair reflects approximately 1 month of growth. Therefore, with hair lengths of several centimeters, we were able to assess the change of time in hormonal activity, with the closest hair to the scalp representing the most recent hormone accumulation [63,64].

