**Report on children**				
	Sociodemographic	Age, sex, race or ethnicity, disabilities, home language, and language proficiency	Parent and teacher	Before intervention
	Adversity	Adverse Childhood Experiences Questionnaire	Parent	Before intervention
	Social-emotional behavior	Children’s Behavior Questionnaire– very short form Strengths and Difficulties Questionnaire Open-ended questions^a^	Parent and teacher	Before intervention, after intervention, and follow-up
	Relationship and implicit bias	Student-Teacher Relationship Scale–short form Preschool expulsion risk measure Open-ended questionsa	Teacher	Before intervention, after intervention, and follow-up

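### Social-emotional and cognitive factors are presented as mechanisms, but no scored measure of them falls between baseline and the week-16 outcome

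*Protocol article*

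**What the plan says.** The hypothesis closing the Background section is that the program could change preschoolers' "behavioral difficulties by impacting physiological, social-emotional, and cognitive factors, which, in turn, could affect teacher outcomes". Social-emotional and cognitive factors thus stand between the program and behavior.

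The second of the three primary aims (Effects on Mechanisms and Outcomes) covers self-regulation, SEL skills, problem behavior and prosocial behavior, and adds "identifying underlying physiological mechanisms of program effects at the midpoint, postintervention time point, and 2-month follow-up". The same section says: "Physiological data were collected after each MMP component, allowing for the evaluation of the effects of sequential implementation on physiological responses". Program Implementation, introducing Table 3, goes further. It says the staged introduction of components allowed their effects on both physiological and SEL mechanisms to be assessed.

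The measurement schedule is spread over several sections:

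- Data Collection Timeline: "Behavioral assessments were administered at all time points except for the midintervention time point". It also says survey data were collected at each time point, without naming scales.
- Table 4: the Children's Behavior Questionnaire (CBQ) and the Strengths and Difficulties Questionnaire (SDQ) are listed as "Before intervention, after intervention, and follow-up". The footnote that adds the midpoint is attached to the open-ended questions.
- HRV Measurement: before the intervention, "every 4 weeks during implementation (with each new module), and at postintervention and 2-month follow-up assessments".
- Hormone Measurements: "Hair samples were collected at 3 time points: preintervention, postintervention, and 2-month follow-up time points", and "A 1-cm section of hair reflects approximately 1 month of growth".

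**The concern.** A mechanism has to change before the outcome it is meant to explain. If both are first measured after baseline at the same visit, their association is the same whether the mechanism moved behavior or behavior moved the mechanism. The staged roll-out could help only if the mechanism were scored between stages.

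At stake is part of a primary aim. The article intends the evidence to support using these assessments in a full-scale trial. An SEL or cognitive pathway reported from this pilot could shape that trial although the data cannot show its direction or which component produced it. The Limitations section does not mention temporal order.

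**Working it through.** **Step 1. Count post-baseline waves before the week-16 outcome.** The inputs are Data Collection Timeline, HRV Measurement, Hormone Measurements and Table 4 with its footnotes.

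| Measure | Scheduled | Waves after baseline and before week 16 |
|---|---|---|
| Behavioral (cognitive) tasks | pre, post, follow-up | 0 |
| Scored CBQ, SDQ and student-teacher relationship scale | pre, post, follow-up | 0 |
| Open-ended questions | also at midpoint | 1 (week 8, not a score) |
| HRV | pre, every 4 weeks, post, follow-up | about 3 (taken as about weeks 4, 8, 12) |
| Hair cuts | pre, post, follow-up | 0 cuts, but segments look back |

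**Step 2. Can the follow-up supply the lag?** One would relate the post value of the mechanism to the follow-up value of the outcome. Data Collection Timeline limits follow-up to one intervention classroom. For the waitlist class, that visit is the end of its own 8-week program. Ordered pairs exist for those children, but no untreated comparison remains. The waitlist class's own 8 weeks also have only a start and an end assessment.

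**Step 3. What does one shared wave allow?** Let X be arm, M the mechanism and Y the outcome, with direct effects left free. The joint density factors in two ways:

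f(M | X) · f(Y | X, M) = f(Y | X) · f(M | X, Y).

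The left side is mechanism first, the right side outcome first. They are the same function, so they must fit equally well. As a check, 4,000 trials were simulated with 22 and 10 children, mechanism truly first and assumed paths of 0.5 SD. The largest log-likelihood difference was about 6 × 10⁻¹⁶, which is rounding error. If full mediation is assumed (no direct effect), the right direction was chosen in 68% of trials, against 50% by chance.

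**Step 4. How large could a false mechanism be?** The article gives no figure, so this is conditional on assumed correlations. Suppose the true order is program → behavior (effect d SD) → SEL or cognitive score, with within-arm correlation r. A same-visit product-of-coefficients analysis finds program → score = r·d and score → behavior given arm = r. The indirect effect is r²·d, so the apparent mediated share is r²: 0.3² = 9%, 0.5² = 25%, 0.6² = 36%. The true share is 0%.

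**Step 5. Can change be credited to a component?** In Table 3, movement starts in week 1, breathwork in week 5, feelings circles in week 9 and the calming corner in week 13. The only scored post-baseline value before follow-up comes after all four have started. One value cannot be divided among four components. The waitlist class likewise receives all four, at 2-week steps, before its final assessment.

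**Step 6. Are mechanism and outcome different measures?** CBQ and SDQ are the only scored questionnaires under social-emotional behavior in Table 4. The SDQ yields both the difficulties and the prosocial scores. No section says which subscale is SEL mechanism and which is behavior outcome.

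**Step 7. Which physiological values do precede the outcome?** HRV does, by Step 1. For hair, 16 weeks × 7 / 30.4 = 3.7 months, or about 3.7 cm, and 8 weeks is about 1.8 cm. In the postintervention sample, program weeks 1-8 therefore lie about 2-4 cm from the scalp.

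**The case against.** The strongest objection concerns physiology. A reader might infer that all proposed mechanisms, cortisol and HRV included, are measured only alongside the outcomes, so that no mechanism claim could survive. The documents do not support that. Program Implementation names respiratory sinus arrhythmia and vagal efficiency as the physiological mechanisms. These come from HRV, which is recorded every 4 weeks during implementation. Hair segments reach back over earlier months, and the article says it relies on that. Nor does it lay out a same-visit cortisol mediation analysis. That part of the objection stands.

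A reader might also infer that SEL mechanism and behavior outcome necessarily come from the same form, rater and sitting. That is not established. Parents and teachers both complete CBQ and SDQ, and direct tasks cover self-regulation and turn-taking, so cross-source analysis is possible. It reduces shared-rater bias but does not change the timing.

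The mechanism work is described as exploratory and preliminary. Data Analysis names only t tests and linear regression, and a mediation model may sit in an analysis plan not shown. This tempers the weight of the point. It does not answer it, because no analysis plan can create a wave that was not collected.

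Finally, the midpoint in the second aim may be meant only for physiological mechanisms, which HRV serves. The sentence can be read either way, which is a reason to clarify it. The SEL claim in Program Implementation does not depend on that reading.

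**Conclusion.** The point holds for the scored SEL and cognitive measures. They have zero post-baseline values before the week-16 outcome, and the follow-up does not repair this. For these links the data cannot separate mechanism from consequence or attribute change to a component. The article's wording claims a property the design lacks.

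This rests on reading the Table 4 footnote as covering only the open-ended questions. If scored scales were in fact given at the midpoint, as the general sentence in Data Collection Timeline could suggest, the questionnaire part would weaken. The task part would not. The 9% to 36% range depends on assumed correlations and on an analysis the article does not specify. It illustrates the risk and is not a predicted result.

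The timing problem does not apply to HRV or segmented hair. Correct order there does not remove confounding, and the text does not say whether the waitlist class had 4-weekly HRV while waiting.

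**What to change.** 1. In the Background hypothesis, the second aim and Program Implementation, drop mechanism and component-effect wording for scored SEL and cognitive measures. Report them as parallel outcomes or exploratory associations.
2. Reconcile the midpoint in the second aim with Data Collection Timeline and Table 4, stating which measures were taken then.
3. Add temporal order to the Limitations section.
4. Restrict any lagged mechanism analysis to physiological values that precede the outcome: module-day HRV, and the postintervention hair segment about 2-4 cm from the scalp (roughly program weeks 1-8). Adjust for baseline and label the analysis exploratory.

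Collection is complete and the article says data are still being processed, so these changes affect wording and analysis choices only. The cost is a narrower mechanism claim. Children with short hair drop out of the lagged hair analysis, and lagged HRV may be usable only in the intervention arm.
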